## Abstract

**Background:**

Asthma is a chronic inflammatory airway disease characterized by reversible obstruction, inflammation and hyperresponsiveness to different stimulus. Aerobic and breathing exercises have been demonstrated to benefit asthmatic patients; however, there is no evidence comparing the effectiveness of these treatments.

**Methods/design:**

This is a prospective, comparative, blinded, and randomized clinical trial with 2 groups that will receive distinct interventions. Forty-eight asthmatic adults with optimized medical treatment will be randomly divided into either aerobic (AG) or breathing exercises (BG). Patients will perform breathing or aerobic exercise twice a week for 3 months, totalizing 24 sessions of 40 minutes each. Before intervention, both groups will complete an educational program consisting of 2 educational classes. Before and after interventions, the following parameters will be quantified: clinical control (main outcome), health related quality of life, levels of anxiety and depression, daily living physical activity and maximal exercise capacity (secondary outcome). Hyperventilation syndrome symptoms, autonomic nervous imbalance, thoracoabdominal kinematics, inflammatory cells in the sputum, fraction of exhaled nitric oxide (FE_NO_) and systemic inflammatory cytokines will also be evaluated as possible mechanisms to explain the benefits of both interventions.

**Discussion:**

Although the benefits of breathing and aerobic exercises have been extensively studied, the comparison between both has never been investigated. Furthermore, the findings of our results will allow us to understand its application and suitability to patients that will have more benefits for every intervention optimizing its effect.

**Trial registration:**

Clinicaltrials.gov; Identifier: NCT02065258.

## Background

Asthma is a chronic inflammatory disorder of the airways that involves many cells and cellular elements. The disease severity can be classified as intermittent or persistent (mild, moderate or severe), and this classification considers the presence of diurnal and nocturnal symptoms, necessity of medication, frequency of exacerbation, physical activity limitations and pulmonary function
[1]. The chronic inflammation is associated with airway hyperresponsiveness and airflow obstruction, which lead to recurrent episodes of wheezing, breathlessness, chest tightness and coughing, particularly at night or in the early morning. All of these symptoms deteriorate in the patient’s quality of life and psychological well-being and restrict daily living physical activities (DLPA)
[2].

The asthma symptoms experienced during DLPA or the fear of triggering symptoms may keep asthmatic subjects from engaging in physical exercise, and the patients tend to be less physically active and less conditioned than healthy individuals
[3]. In addition, asthmatic patients have higher levels of anxiety and depression that have been shown to be associated with an increased number of exacerbations
[4] and the diagnosis of severe asthma
[5]. These psychosocial disorders can modify the respiratory breathing pattern, which leads to irregular breathing, frequent sighing, and predominant thoracic breathing
[6]. These irregular breathing patterns increase the number of respiratory (breathlessness, chest tightness and pain) and non-respiratory symptoms (anxiety, dizziness and fatigue)
[7].

Asthma does not have a cure but its clinical manifestations can be controlled with the appropriate treatment. The goal for asthma treatment is to achieve and maintain asthma control, and the treatment is based on medication (controllers and relievers). Clinical control is defined as an effective management of the characteristics of the disease, which include control of the following symptoms: nocturnal awakening, reliever use and activity limitation
[8]. However, recent studies have also shown that non-medicinal treatments are important adjuvants in asthma treatment, and the main techniques used worldwide are aerobic
[9] and breathing exercises
[10].

There is evidence suggesting that aerobic training improves fitness and health related quality of life (HRQoL)
[11]. Additionally, aerobic training reduces psychosocial distress
[2], exercise-induced bronchoconstriction
[12] and corticosteroid consumption
[13], exacerbation episodes and asthma symptoms
[13]. Moreover, breathing exercises have been shown to improve HRQoL
[14] and expiratory peak flow values
[15]. Breathing exercises also reduce the levels of anxiety and depression
[16], asthma symptoms
[17], the use of relief medication
[14], exacerbation episodes and airway hyperresponsiveness
[18].

The research questions were:Which exercise intervention is more effective to improve clinical control in patients with moderate and severe asthma?Which are the mechanisms involved to improve clinical control in both interventions?

## Method

### Design

This trial was designed as a prospective, comparative, blinded, and randomized clinical trial with 2 groups that will receive distinct interventions. See the study design in Figure 
1.

**Figure 1 Fig1:**
[figure not shown]
**Study flow chart: after inclusion, patients will be evaluated twice.** In visit one clinical control, pulmonary and systemic inflammation and psychosocial variables will be measured and in visit two pulmonary function, maximal exercise capacity, thoracoabdominal kinematics and autonomic control will be assessed; afterwards subjects will begin the educational program, consisting of two classes: one related to the disease and skills concerning medication and self-monitoring, and other related to control of external factors and peak flow meter usage. Only then, subjects will be randomized into aerobic or breathing group for 24 sessions, after which they will be revaluated.

### Participants, therapists, centers

#### Study setting

Patients will be recruited from an outpatient clinic that assists moderate and severe asthmatic patients in an University Hospital. The Clinics Hospital Ethics Committee approved the study (0097/10). All participants gave written informed consent before data collection began.

### Allocation and randomization

Eligible patients will be randomized to either breathing or aerobic exercise interventions. The randomization schedule was computer-generated by the chief investigator who will not be involved in the recruitment or treatment of the patients.

### Eligibility criteria

The Hospital Ethics Committee approved the study and patients must provide written informed consent before any study procedures be performed. Asthma diagnosis and treatment will be based on the guidelines of the Global Initiative for Asthma
[19].

#### Inclusion criteria

Age between 25 and 65 years-old; both genders; body mass index (BMI) <35 Kg/m^2^; sedentary (currently doing < 60 minutes of structured/planned physical activity per week); medical treatment for at least 6 months; and clinically stable (i.e., no crises or changes in medication for ≥30 days).

#### Exclusion criteria

*S*mokers; participants in another research protocol; patients that are incapable of exercising; unable to understand any questionnaire; any other medical condition that confers greater morbidity than asthma (e.g., active cancer) which will be confirmed by physician review; currently pregnant.

### Intervention

#### Educational program

Before the interventions, both groups will complete an educational program that consists of 2 classes performed once a week and lasting 2 hours each. Presentations and group discussions will include information about asthma pathophysiology, medication skills, self-monitoring techniques, and environmental control and avoidance strategies according to previous studies
[2] and asthma guidelines
[19].

### Aerobic training program

It will be performed on a treadmill with an initial intensity of 60% and reaching a maximum intensity of 80% of the predicted heart rate during training. The intensity values will be calculated using Karvonen’s formula
[20] (1957). Exercise intensity will be increased if the patient does not experience an increase in asthma symptoms during the exercise for 2 consecutive training days. Before and after every session, patients will perform a peak expiratory flow test. If these values are lower than 70% of the patient’s maximum value, then the patient will be advised to use the rescue dose of a bronchodilator prescribed their physician. All of the aerobic training details have been previously described elsewhere
[13].

### Breathing exercise

Breathing exercise will be based on Yoga’s breathing techniques
[21] and will focus on stimulating nasal and diaphragmatic breathing, increasing the expiratory time, slowing the respiratory flow and regulating the breathing rhythm. Breathing exercises will be divided into 3 phases (lasting one month each) with an intensity progression every 8 sessions (Table 
1).

**Table 1 Tab1:** **Breathing exercise program**

1st phase		
Exercise	Duration	Repetition
*Lying position*		
Raise right arm, left arm and then both, stretching the intercostal muscles	20 s	2
Pull right knee, left knee and then both, stretching paraspinal muscles	20 s	2
Turn hip to the side, keeping your shoulders flat on the mat. One hand holds the knee while lifting up the other arm	20 s	1 each side
Lateral decubitus, one arm supporting the head and other remains draped over the body. Inspiring, rise the arm above the head, eeturning to the starting position, at expiration	1 breath	4 each side
Keep an outstretched arm, while making three deep breaths, return.	20 s	1 each side
Inspire holding knees and pull them toward your chest as you exhale	1 breath	4
With the body length, holding the head with hands and take them towards the chest	20 s	1
*Sitting*		
With your legs extended and stretch the posterior muscles, leading arms outstretched to the feet	20 s	1
Stretch intercostal muscles and obliques, and raising arm laterally flexing the trunk	20 s	2 each side
Introduction to the breathing exercise with hands on abdomen and the diaphragmatic stimulation with active expiration	1 breath	10
Kapalabhati - quick expirations generated by vigorous contraction of the rectus abdominis	1 breath	3 series of 30
With your legs extended and stretch the posterior muscles, leading arms outstretched to the feet	20 s	1
**2nd phase**		
**Exercise**	**Duration**	**Repetition**
*Lying position*		
Raise right arm, left arm and then both, stretching the intercostal muscles	20 s	1
Pull right knee, left knee and then both, stretching paraspinal muscles	20 s	1
Lateral decubitus, one arm supporting the head and other remains draped over the body. Inspiring, rise the arm above the head, returning to the starting position, at expiration	1 breath	4 each side
Keep an outstretched arm, while making three deep breaths, return.	20 s	1 each side
Boat adapted: feet flat, knees bent and hands on his thigh, inhale deeply and take hands toward the knees contracting the abdomen	1 breath	4
Inspire holding knees and pull them toward your chest as you exhale	1 breath	4
Preparation Uddhiyana: arms along the body raise the arms in inspiration, expiration returns	1 breath	4
Preparation Uddhiana: actively inhale and exhale, and apnea raise and lower arms	5 s	4
*Sitting*		
With your legs extended and stretch the posterior muscles, leading arms outstretched to the feet	20 s	1
Preparation Uddhiyana: raise the arms sideways in inspiration and return in expiration	1 breath	4
Preparation Uddhiana: actively inhale and exhale, and apnea raise and lower arms	5 s	4
Uddhiyana Bandha: complete expiration followed by inspiratory effort in the presence of apnea	5 s	1
Uddhiyana Bandha + Kapalabhati	1 breath	3 series of 1 and 45
With your legs extended and stretch the posterior muscles, leading arms outstretched to the feet	20 s	1
**3rd phase**		
**Exercise**	**Duration**	**Repetition**
*Lying position*		
Raise right arm, left arm and then both, stretching the intercostal muscles	20 s	1
Pull right knee, left knee and then both, stretching paraspinal muscles	20 s	1
Lateral decubitus, one arm supporting the head and other remains draped over the body. Inspiring, rise the arm above the head, returning to the starting position, at expiration	1 breath	4 each side
Keep an outstretched arm, while making three deep breaths, return.	20 s	1 each side
Boat adapted: feet flat, knees bent and hands on his thigh, inhale deeply and take hands toward the knees contracting the abdomen	1 breath	4
Inspire holding knees and pull them toward your chest as you exhale	1 breath	4
*Sitting*		
With your legs extended and stretch the posterior muscles, leading arms outstretched to the feet	20 s	1
Uddhiyana Bandha + Kapalabhati	5 s and 1 breath	2 series of 1 and 60
Surya bedhana: inhale through the right nostril, take head towards the chest in apnea returns to the starting position and exhale through the left nostril.	5 s	1 each side
Surya bedhana + Kapalabhati	5 s and 1 breath	2 series of 1 and 70
With your legs extended and stretch the posterior muscles, leading arms outstretched to the feet	20 s	1

All participants will be required to maintain their normal medical regimens during the interventions.

### Outcome measures

#### Primary outcome

The asthma control questionnaire (ACQ)
[22] will be used to assess asthma control. We will compare the differences between the 2 interventions in the absolute change in asthma control post-intervention. This questionnaire is validated to measure asthma control in adult patients and have been validated to Brazilian Portuguese
[23]. ACQ is a simple instrument and is easy to use that quantifies the following asthma symptoms: nocturnal and morning symptoms, limitation of daily activities, dyspnea and wheezing, and the use of medication (short-acting β_2_-agonist). Patient’s will be scored on a scale ranging from 0 to 6 (0 = without limitation and 6 = maximum limitation). The clinical score of forced expiratory volume (% of predicted, pre-bronchodilator) will be scored on similar scale. The items will be calculated, and the scores of the ACQ will be the average from 7 items between 0 (fully controlled) and 6 (severely uncontrolled). The cutoff will be adopted from previously developed studies, considering controlled (ACQ <0.75 points), not well controlled or poorly controlled asthma (ACQ > 1.5 points). A clinically effective treatment results in a 0.5 point decrease in the score after the intervention
[24].

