#### Secondary outcomes

##### Psychosocial morbidity

The asthma quality of life questionnaire (AQLQ)
[25] and the hospital anxiety and depression (HAD) scale
[26] will be used to assess psychosocial morbidity. We will compare the differences between both interventions in the absolute values. AQLQ is a questionnaire divided into the following 4 domains: physical limitation, frequency of symptoms, socioeconomic, and psychosocial. Each domain has a maximum score of 33, 6, 11, and 7 points, respectively that will be converted into percentages, where higher scores represent better HRQoL. The HAD has 14 items divided into 2 subscales (7 for anxiety (HAD-A) and 7 for depression (HAD-D)). For each item, there are 4 alternatives, ranging in score from 0 to 3. The sum of each subscale score ranges from 0 to 21. The cutoff value for anxiety and depression is 8 and 9, respectively.

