### Data analysis

#### Sample size

It was estimated based on a minimal important difference of 0.5 points on the ACQ questionnaire with a standard deviation of 0.72
[38]. A sample size of 40 patients was required for a 5% level of significance with 80% power using a two-tailed *t* test. An estimated drop-out rate of 20% was used to determine the final target sample size of 48 patients.

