#### Proposed statistical analyses

Data normality will be evaluated with the Kolmogorov-Smirnov test. The comparison of the clinical control and other variables will be made by a two-way analysis of variance (ANOVA) with repeated measures followed by the Student-Newman Keuls post-hoc test to identify significant differences. The level of statistical significance will be set at 5% (p < 0.05).

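### The primary ACQ comparison is fixed as an unadjusted change analysis; adjusting for the pre-randomization ACQ already collected would be valid too, and more precise

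*Protocol article*

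**What the plan says.** Under Primary outcome, the protocol article states: "We will compare the differences between the 2 interventions in the absolute change in asthma control post-intervention". Under Proposed statistical analyses, the model for clinical control and the other variables is a "two-way analysis of variance (ANOVA) with repeated measures followed by the Student-Newman Keuls post-hoc test". Neither section names the baseline value as a covariate.

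The legend of Figure 1 gives the timing: "In visit one clinical control, pulmonary and systemic inflammation and psychosocial variables will be measured". The education classes follow, and randomization comes only after them. Baseline ACQ is therefore a pre-randomization measurement.

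The Sample size section rests on a "minimal important difference of 0.5 points on the ACQ questionnaire with a standard deviation of 0.72" and does not say whether that SD belongs to the score or to its change. For AQLQ and HAD, the Psychosocial morbidity section says: "We will compare the differences between both interventions in the absolute values".

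**The concern.** The method is stated, so this is not a detail left to an analysis plan that is not shown. A change-score comparison fixes the coefficient on baseline at 1. When the pre-post correlation is below 1 (with similar SDs before and after), the best-fitting coefficient is smaller. Subtracting the whole baseline then adds noise and over-corrects for any chance difference between arms at entry.

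In a trial that plans for 40 evaluable patients, the precision given up can be appreciable. A baseline difference that arises by chance could also move the estimate by a visible fraction of the 0.5-point threshold. Both can be avoided with data the trial already collects.

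**Working it through.** **Inputs.** From the Sample size section: difference 0.5, SD 0.72, two-sided 5%, 40 evaluable patients, target 48. Assumed: 1:1 allocation (20 per arm evaluable, 24 per arm randomized), equal SD s before and after, and rho = 0.3 to 0.95.

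**The plan's own figure.** The protocol says "A sample size of 40 patients was required for a 5% level of significance with 80% power".
- If 0.72 is the SD of the quantity tested, n per arm = 2 × (1.96 + 0.84)² × 0.72² / 0.5² = 32.6, so 33 per arm or 66 in total (34 per arm by exact t). Power at 20 per arm is 57% by exact t. The figure of 40 is not reproduced.
- If 0.72 is the SD of the score and rho = 0.7, the SD of change is 0.72 × √(2 × 0.3) = 0.558. Then n = 19.5 per arm, so 20 per arm or 40 in total, with 79% power by exact t. The figure is reproduced.

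The text does not settle which reading applies, so both are carried forward.

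**Variance.**
- Change score: 2s²(1 − rho).
- Baseline-adjusted: s²(1 − rho²).
- Ratio: (1 + rho)/2 = 0.65, 0.75, 0.85 and 0.95 at rho 0.3, 0.5, 0.7 and 0.9.
- Estimating the slope costs a factor of about 1 + 1/(40 − 4). The ratios become about 0.67, 0.77, 0.87 and 0.98, and about 1.00 at rho 0.95.

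**Power for 0.5 points at 20 per arm.** Change-score figures are exact t; adjusted figures are simulated and include the cost of the slope.

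| rho | 0.72 = SD of change: change → adjusted | 0.72 = SD of score: change → adjusted |
|---|---|---|
| 0.3 | 57% → 74% | 44% → 60% |
| 0.5 | 57% → 68% | 57% → 68% |
| 0.7 | 57% → 63% | 79% → 84% |
| 0.9 | 57% → 58% | above 99% for both |

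At rho 0.95 there is no gain. In simulation both methods hold a type I error of about 5%. In the middle column, holding the SD of change at 0.72 means that the score SD varies with rho (0.61 at rho 0.3, 0.93 at rho 0.7), so its rows describe different populations.

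**Chance imbalance.** Given an observed baseline difference D between arms, the change-score estimate is off by −(1 − rho) × D.
- For D = 0.3 points: −0.21, −0.15 and −0.09 at rho 0.3, 0.5 and 0.7.
- If 0.72 is the score SD, one standard error of D at 24 per arm is 0.72 × √(2/24) = 0.21. At rho 0.5 the shift is 0.5 × 0.21 ≈ 0.10, a fifth of the 0.5-point threshold.
- In simulation with a true effect of −0.5 and an imbalance above one standard error, change scores averaged −0.70, −0.68 and −0.63 at rho 0.3, 0.5 and 0.7. The adjusted estimate stayed at about −0.50.

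**The case against.** The strongest reply is that nothing here is invalid. In a randomized trial the change-score comparison is unbiased over randomizations and keeps its 5% level, and a condensed article often leaves covariates to the analysis plan. The first part stands: this is a matter of efficiency. The second part carries less weight, because the article does name its model.

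The sentence under Primary outcome is also not wrong. Change can remain the reported outcome, because regressing change on arm and baseline gives the same treatment effect as regressing the post-intervention score on arm and baseline. Only the model needs to change.

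A reader might infer more from the documents than they support:
- **That the planned analysis is biased.** The shift is conditional on an observed imbalance and averages to zero over randomizations.
- **That the trial is shown to be short of power, and adjustment is the only remedy.** That depends on which SD 0.72 is and on rho; one reading gives the planned 40. Better retention would also help.
- **That the outcomes are analysed on different scales.** The AQLQ and HAD wording is loose, but the analysis section applies one model to all variables.

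Finally, the change is more than a wording edit. The Study status section says data are still being analysed, so a new primary model could look data-driven unless it is dated and documented.

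**Conclusion.** The point holds as an avoidable inefficiency in a stated method. For rho between 0.3 and 0.7, baseline adjustment lowers the variance of the primary estimate by about 13% to 33% at 40 patients. It raises power by about 6 to 17 percentage points if 0.72 is the SD of change, and by about 5 to 16 if it is the SD of the score. The gain is about one point or less at rho 0.9 and is gone near 0.95. If 0.72 is the SD of change, adjustment alone does not bring power to 80% at 20 per arm for any rho from 0.3 upward.

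The size rests on rho, which the documents do not give, on equal variances before and after, and on 1:1 allocation. The direction of the gain is the same under both readings of the SD. The change is worth making, but the planned analysis would not be invalid without it.

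**What to change.** In Proposed statistical analyses, make the primary analysis a linear model of ACQ (post-intervention score or change) on arm and baseline ACQ. Report the adjusted between-arm difference with its 95% confidence interval. Use the same form for the other outcomes measured before and after, transforming skewed biomarkers such as cytokines, FeNO and sputum cell counts where needed. Bring the AQLQ and HAD wording under Psychosocial morbidity into line. The Primary outcome section can keep change as the reported quantity.

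The cost is one degree of freedom and no new data. Because analysis is under way, the change needs a dated amendment made before any between-arm ACQ comparison is seen. If one has already been seen, keep the planned analysis as primary and report the adjusted model as a declared supplementary analysis.

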#### Secondary outcomes

##### Psychosocial morbidity

The asthma quality of life questionnaire (AQLQ)
[25] and the hospital anxiety and depression (HAD) scale
[26] will be used to assess psychosocial morbidity. We will compare the differences between both interventions in the absolute values. AQLQ is a questionnaire divided into the following 4 domains: physical limitation, frequency of symptoms, socioeconomic, and psychosocial. Each domain has a maximum score of 33, 6, 11, and 7 points, respectively that will be converted into percentages, where higher scores represent better HRQoL. The HAD has 14 items divided into 2 subscales (7 for anxiety (HAD-A) and 7 for depression (HAD-D)). For each item, there are 4 alternatives, ranging in score from 0 to 3. The sum of each subscale score ranges from 0 to 21. The cutoff value for anxiety and depression is 8 and 9, respectively.

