##### Daily living physical activity (DLPA)

An accelerometer (Power Walker SW 610, Japan) will quantify the absolute change in DLPA. The accelerometer records the total daily number of steps, the number of steps performed at moderate intensity (≥110 steps per minute) and the time spent during DLPA. The assessment will be performed over a period of 7 days, and the DLPA will be quantified before and after the interventions. The accelerometer automatically records the total number of steps during the 7 days, and each patient will record their amount of moderate intensity DLPA in a dairy. The accelerometer will be used to average the number of steps performed during the 5 day period (disregarding the first and last days)
[27].

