##### Maximal exercise capacity

Shuttle walking test
[28] will assess exercise capacity and it will compare the absolute change in maximal exercise capacity post-intervention. Cones set up in a corridor will demarcate 10 meters, and the patients will be asked to walk around the cones at a speed pre-determined by sound signals. The sound signals indicate the moment when the patient must round the cone, and the speed increases at a rate of 0.6 km/h per minute. The total protocol consists of 12 stages, and the test can be discontinued by the individual or the therapist if the patient is unable to maintain the speed required to complete the stage (distance greater than 0.5 m from the cone). The test will be discontinued if the patient present chest pain, intolerable dyspnea, dizziness, cramps, leg pain or pallor. Patient’s heart and respiratory rates, blood pressure, dyspnea and leg fatigue will be measured before and after the test. The scale of perceived exertion
[29] will be used to measure dyspnea and leg fatigue.

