### Other notable outcomes – possible mechanisms

#### Hyperventilation syndrome symptoms

Nijmegen questionnaire will be used to assess hyperventilation symptoms. We will compare the differences between the 2 treatments in the absolute change in hyperventilation symptoms post-intervention. The Nijmegen questionnaire is composed of 16 questions that quantify abnormal breathing; (each question range in scale from 0 (never) to 4 (very often)). A total score of ≥23 establishes hyperventilation syndrome with a sensitivity of 91% and a specificity of 95%
[32].

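### The contrast for AQLQ and HAD is worded differently from the other outcomes and left open: one valid reading ignores the baseline, another halves the effect

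*Protocol article*

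**What the plan says.** The Psychosocial morbidity section, which covers the four AQLQ domains and the two HAD subscales, says: "We will compare the differences between both interventions in the absolute values". It gives no time point and does not mention change.

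Four other sections name change:

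- Primary outcome (ACQ): "We will compare the differences between the 2 interventions in the absolute change in asthma control post-intervention".
- Daily living physical activity: the accelerometer "will quantify the absolute change in DLPA".
- Maximal exercise capacity: "it will compare the absolute change in maximal exercise capacity post-intervention".
- Hyperventilation syndrome symptoms: "We will compare the differences between the 2 treatments in the absolute change in hyperventilation symptoms post-intervention".

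The abstract has quality of life, anxiety and depression assessed at both times: "Before and after interventions, the following parameters will be quantified". The Proposed statistical analyses section gives one method for everything: "The comparison of the clinical control and other variables will be made by a two-way analysis of variance (ANOVA) with repeated measures", followed by Student-Newman-Keuls post-hoc tests. It does not say whether the arm, time or arm-by-time term answers the question.

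**The concern.** The sentences for ACQ, for AQLQ and HAD, and for hyperventilation symptoms are built almost identically. Only the AQLQ and HAD sentence replaces change with values, and no reason is given. The ANOVA does not settle the matter, because it contains every candidate contrast:

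- the arm-by-time term compares change;
- the arm main effect compares values averaged over both visits;
- the post-hoc tests can compare post-intervention cell means.

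Six secondary scores are affected. They matter to the second research question, on mechanisms, because the Discussion expects breathing exercise to work through lower anxiety and depression. With 20 to 24 patients per arm, the choice of contrast can decide whether a result falls below p = 0.05.

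**Working it through.** **Inputs from the article.** Two randomised arms ("Eligible patients will be randomized to either breathing or aerobic exercise interventions"), one assessment before and one after, 48 patients randomised, 40 required for analysis, two-sided 5% level. No effect size or power is stated for AQLQ or HAD, so there is no figure of the plan's own to reproduce on this point.

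**Assumptions.** Equal allocation (24 per arm, or 20 per arm after losses), equal SD before and after (set to 1), true effect d = 0.6 SD, and pre-post correlation r from 0.3 to 0.8.

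**What each reading estimates** (per-patient variance, in units of SD²):

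- Post-intervention score: effect d, variance 1.
- Change (arm-by-time term): effect d, variance 2(1 − r).
- Arm main effect (mean of pre and post): effect d/2, variance (1 + r)/2.
- Post score adjusted for baseline: effect d, variance 1 − r².

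Adjusting the change for baseline gives the same arm effect as adjusting the post score, because subtracting the baseline from both sides of the model alters only the baseline slope.

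**Standardised effects at r = 0.7:**

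- Post: 0.6/√1 = 0.600.
- Change: 0.6/√0.6 = 0.775.
- Main effect: 0.3/√0.85 = 0.325.
- Adjusted: 0.6/√0.51 = 0.840.

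Multiplying by √(24/2) = 3.464 gives noncentralities of 2.08, 2.68, 1.13 and 2.91. Power follows from the noncentral t distribution with 46 degrees of freedom (45 when adjusted).

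| Per arm | r | Post | Change | Main effect | Adjusted |
|---|---|---|---|---|---|
| 24 | 0.3 | 53.0% | 40.5% | 24.3% | 56.8% |
| 24 | 0.5 | 53.0% | 53.0% | 21.7% | 65.1% |
| 24 | 0.6 | 53.0% | 62.4% | 20.6% | 72.0% |
| 24 | 0.7 | 53.0% | 74.8% | 19.7% | 81.3% |
| 24 | 0.8 | 53.0% | 89.6% | 18.9% | 92.4% |
| 20 | 0.7 | 45.6% | 66.5% | 17.1% | 73.5% |

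Simulation with 20,000 trials per setting at 24 per arm agrees to within about one percentage point.

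**Why adjustment is safe whatever r is.** Its variance is below that of post scores by 1 − (1 − r²) = r², and below that of change by 2(1 − r) − (1 − r²) = (1 − r)². Neither difference can be negative. The cost is one degree of freedom and a small term for chance baseline imbalance.

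**Chance baseline gaps.** The SE of the baseline difference between arms is √(2/24) = 0.29 SD, or √(2/20) = 0.32 SD. A gap above 0.3 SD arises in 30% to 34% of trials. Given a gap D, the expected post-score difference shifts by rD and the change difference by −(1 − r)D. At r = 0.7 and D = 0.3 these are +0.21 and −0.09 SD; the adjusted difference does not shift.

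**Agreement between readings** (24 per arm, d = 0.6, r = 0.7). Post and change tests disagree on significance in about 39% of simulated trials, and main-effect and change tests in about 65%.

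**The case against.** The strongest reply is that the Psychosocial morbidity sentence fixes no test at all. The only method in the article is the repeated-measures ANOVA, it covers these outcomes, and with two visits its arm-by-time term is the comparison of change. The wording may simply mean absolute rather than percentage differences. A condensed article may also leave the deciding term to the analysis plan. Much of this stands: silence on the deciding term would not be a finding by itself. What remains is that the one sentence describing the AQLQ and HAD contrast points away from the change named elsewhere, and nothing in the article reconciles the two.

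A reader might infer several stronger things that the article does not support:

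- **That the stated contrast is wrong.** Under randomisation a comparison of post scores is unbiased and keeps its 5% error rate. In simulation at a true effect of 0.5 SD, post scores and change both averaged 0.50. Post scores are the more precise when r is below 0.5.
- **That the plan adopts the arm main effect.** This is one construction of vague text. No section says the two visits will be averaged.
- **That the conclusion could reverse.** What varies is significant versus not significant. Significant results in opposite directions for post and change occurred in at most 0.02% of simulated trials.
- **That false positives nearly double.** Accepting whichever of two contrasts is significant would give 9% to 10%, but only if the choice follows sight of the data. The article proposes no such choice.

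**Conclusion.** The point holds as an unresolved inconsistency in the secondary outcomes, and the primary ACQ conclusion is untouched. The AQLQ and HAD wording differs from the change named for four other outcomes, and the ANOVA does not say which term decides. The post-score reading is legitimate but wastes the baseline. The main-effect reading would dilute the effect by half and has the lowest power at every correlation examined.

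The size depends on assumptions the article does not supply. At 0.6 SD, 24 per arm and r = 0.7, power runs from about 20% (main effect) through 53% (post) and 75% (change) to 81% (adjusted). The ordering of post and change turns over at r = 0.5, so the case for change over post scores is not general. The case for baseline adjustment is: it is at least as precise as either, apart from a trivial loss of degrees of freedom.

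**What to change.** In the Psychosocial morbidity section, state that each AQLQ domain and HAD subscale is compared between arms on the post-intervention score (equivalently, the change) adjusted for its own baseline by ANCOVA. If the repeated-measures ANOVA is kept, state instead that the arm-by-time term decides. In either case, add that the arm main effect is not used for inference.

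This costs one or two sentences and needs no new data or patients. The Study status section says that data are already being analysed, so the clarification should be dated and should record whether results by arm had been seen.
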